### Communication of Findings

As we have registered the trial on ClinicalTrials.gov, once data collection is complete, we will report the results on ClinicalTrials.gov, including a flow chart of study recruitment and dropout, baseline characteristics of participants, and primary and secondary outcomes. We will share the findings from this study in the form of abstracts, as well as oral and poster presentations at national and international conferences related to exercise and physical activity (eg, Canadian Society for Exercise Physiology or American College of Sports Medicine annual meetings). We also intend to publish our findings in peer-reviewed journals. Three months following the completion of data collection, the research team will create a combined (both sites) deidentified dataset, including a codebook with the variables outlined in this protocol that will be used for statistical analysis. This deidentified codebook will be stored at UBC Okanagan on a secured Microsoft Teams channel with access controlled to study personnel listed on the ethics approval. The PI will share a deidentified dataset with outside investigators upon reasonable request according to the policies in the approved UBC Clinical Research Ethics Board protocol.

### Study Withdrawal

Participants will be instructed during the first study visit that they may withdraw from the study at any point and can do so by communicating to the research team (using any method) that they would like to withdraw. The data collected up to the point of withdrawal will be included in the analysis, and the reason for withdrawal will be recorded.

### Statistical Analysis

The proportion of eligible participants who consent to participate will be presented by site and overall, along with the proportions in each intervention group completing postintervention testing and the reasons for withdrawal. Descriptive characteristics and outcomes will be summarized overall and by intervention group as mean (SD) for normally distributed continuous variables, median (IQR) for nonnormally distributed continuous variables, and number (percentage) for categorical variables. The exit questionnaire will include open-ended questions to help us explore the barriers and facilitators, assessing which elements of the intervention are most effective for participants. Although inferential statistics are not necessary for pilot trials, we will perform exploratory analyses on outcomes in order to describe between-group treatment effects at 12 weeks with 95% CIs and calculate preliminary effect sizes. Continuous dependent variables will be analyzed using constrained baseline longitudinal analysis via linear mixed models with group and time as fixed effects and participant and study site as random effects [50]. The between-group effect estimate at 12 weeks will be the primary outcome of interest in these exploratory analyses. The data will be analyzed based on the intention-to-treat principle, with the assumption of data missing at random. Exploratory sensitivity analyses based on participants with high, moderate, or low adherence will be explored if appropriate. No interim analysis will be conducted. The statistical analysis plan was posted to the Open Science Framework on April 30, 2026 [51].

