## Methods

### Trial Design

This pilot RCT will involve a parallel-arm design where participants are randomized (1:1 allocation ratio stratified by sex and site) into an exercise snacks or stretching/mobility exercise comparator group for 12 weeks (Figure 1). Target enrollment is 80 participants recruited from Kelowna, BC (University of British Columbia [UBC] Okanagan), and Hamilton, ON (McMaster University), and their surrounding areas using online advertisements supported by a recruitment service agency (Wayturn, Mariefred, Sweden). At each site, potential participants’ contact information is provided to the research team, which will initiate contact to schedule a screening call to determine eligibility before booking the first baseline study visit. Interventions will be delivered at home or work via a custom study mobile app and individualized via onboarding telephone exercise counseling sessions to develop an action plan for incorporating exercise snacks or stretching exercises into participants’ daily routines. Primary outcomes focused on feasibility will be assessed over the course of the intervention, and secondary outcomes focused on efficacy will be assessed at baseline and following the 12-week intervention. A flow diagram for the trial is presented in Figure 1.

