### Participants and Eligibility Criteria

Eligible participants will be living with obesity, currently inactive, and aged between 35 and 64 years. Potentially eligible participants will be contacted via phone or email to complete the eligibility screening, which includes a medical history, self-reported anthropometric measurements, current physical activity behavior, and details of current medications. Once participants have consented to participate, they will be assigned a deidentified code, and all data will be linked to their deidentified code rather than identifying information (eg, name, date of birth, email address). Informed consent forms and any other data collection sheets that contain identifying information will be stored separately from deidentified data.

There are no formal guidelines for determining sample size for a pilot trial, but published simulations suggest that 35 participants per group are appropriate for estimating the pooled SD for normally distributed variables to allow for accurate effect size estimates on outcomes [27]. This sample size is in line with the median sample size for pilot (n=30) and feasibility (n=36) trials in a published audit of registered pilot or feasibility trials [28]. In line with this, we will aim to recruit 40 participants per group (80 participants in total). Detailed inclusion and exclusion criteria are described in Textbox 1; participants will first be screened for these criteria during a screening phone call followed by confirmation during the first laboratory visit (Figure 2).

Textbox 1.Detailed inclusion and exclusion criteria.

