**Secondary outcomes**
Cardiorespiratory fitness estimated from walking treadmill test.Lower body muscular endurance assessed using sit-to-stand test.Upper body maximal strength assessed using hand-grip dynamometer.Waist circumference.Weight.BMI.Fasting plasma glucose.Fasting plasma insulin.Systolic blood pressure.Diastolic blood pressure.Physical activity estimated using accelerometry.

Feasibility outcomes will include the number of participants who are eligible to participate, the number of participants who enroll, the number of participants who are retained at 12-week postintervention testing, as well as the number of 1-minute exercise bouts completed during the intervention. The proportion of participants contacted, screened, and enrolled in the intervention will be recorded, as well as the number of eligible participants who chose not to participate (and reasons why). Adherence will be determined by summing the total number of 1-minute exercise bouts completed during the intervention. The primary adherence outcome will be app-reported adherence, and this will be supplemented (where needed) with participant self-report (via weekly REDCap surveys) for participants who choose to perform movement breaks outside of the app. We will define high, moderate, and low adherence as completing >70%, 50% to 69%, or <50% of the prescribed intervention, respectively. Feasibility is defined as >70% of the participants completing at least 67% of the exercise bouts (ie, >13 weekly bouts) on at least 8 out of 12 weeks.

A modified Balke walking treadmill test will be used to estimate cardiorespiratory fitness [40-42]. To begin, participants will complete a 3-minute warm-up at 3.2 km/h and 0% incline on a motorized treadmill. Upon the completion of the warm-up, the test will begin, and the speed will be increased to 5.3 km/h where it will remain for the remainder of the test, with 1% increases in grade every minute until volitional fatigue. Participants will be familiarized with this test during the first baseline testing visit, and if the test duration is ≤7 minutes, ≥13 minutes, or ≥15 minutes, then the speed for all subsequent tests (visits 2 and 3) will be adjusted to 4.5, 6.1, or 6.9 km/h, respectively. The speed and maximal grade attained on the test will be used to estimate cardiorespiratory fitness using the calculation below [43].

$${VO}_{2\max}\;(mL\;kg^{-1}\;min^{-1})=speed\;(m\;min^{-1})\times \left(0.17+(fractional\;grade\times 0.79)\right)+3.5$$

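### As described, the mixed model assumes equal variance at baseline and week 12 unless the posted SAP sets a freer covariance; an unstructured 2x2 visit covariance would protect the 12-week CI at almost no cost

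*Protocol article*

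**What the plan says.** The Statistical Analysis section specifies "constrained baseline longitudinal analysis via linear mixed models with group and time as fixed effects and participant and study site as random effects". The stated purpose is to "describe between-group treatment effects at 12 weeks with 95% CIs and calculate preliminary effect sizes", and the 12-week between-group estimate is named as the quantity of interest. The section calls these analyses exploratory. It does not state a residual covariance or an equal-variance assumption, and it refers to a statistical analysis plan posted separately, which is not at hand.

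Trial Design fixes two measurement times: "secondary outcomes focused on efficacy will be assessed at baseline and following the 12-week intervention". Allocation is "1:1 allocation ratio stratified by sex and site", with a target of 40 per group.

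The sample size rests on a precision argument (Participants and Eligibility Criteria): "35 participants per group are appropriate for estimating the pooled SD for normally distributed variables to allow for accurate effect size estimates on outcomes". Statistical Analysis promises descriptive summaries overall and by group, with mean (SD) for normally distributed variables but median (IQR) for the others. No section gives an SD at either visit or a within-person correlation.

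**The concern.** With two visits, a participant random intercept plus independent residuals has only two within-site variance parameters: the between-person variance and the residual variance. It therefore gives baseline and week 12 the same total variance. If the true variances differ, the model weights the baseline difference slightly wrongly and, more importantly, computes the wrong standard error for the 12-week contrast.

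The design offers some reason to doubt equality. Eligibility bounds BMI and waist from below at entry, and nothing bounds them at week 12. The plan also expects adherence to vary widely ("We will define high, moderate, and low adherence as completing >70%, 50% to 69%, or <50% of the prescribed intervention"), which could spread week-12 values in the exercise snacks arm.

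At stake is the calibration of the main efficacy interval in a pilot whose second aim (Study Objectives) is to inform effect sizes for a definitive trial.

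**Working it through.** The plan states no SD, correlation or CI width, so there is no published figure to reproduce. The check asks how far the interval is off for a given departure from equal variance.

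**Inputs.** From the article: two visits, 1:1 allocation, 40 per group, constrained baseline, participant random effect. Assumed: independent residuals, baseline SD = 1, week-12 SD = k, within-person correlation r, complete data, site effect omitted.

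**Derivation (large sample).**
1. Compound symmetry fits one variance, v = (1+k²)/2, and one correlation, ρ = rk/v.
2. The variance the model reports for the 12-week difference is proportional to v(1−ρ²).
3. The true variance of the same estimator is proportional to k² − 2ρrk + ρ². Since rk = ρv and 2v − 1 = k², this equals k²(1−ρ²).
4. Hence model SE / true SE = sqrt(v/k²) = sqrt((1+k²)/2)/k. Neither r nor the sample size remains, so a larger trial would not remove the discrepancy.
5. Coverage = 2Φ(1.96 × ratio) − 1.

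| k (assumed) | v/k² | CI width ratio | Coverage |
|---|---|---|---|
| 0.8 | 0.82/0.64 | 1.132 | 97.3% |
| 0.9 | 0.905/0.81 | 1.057 | 96.2% |
| 1.0 | 1/1 | 1.000 | 95.0% |
| 1.1 | 1.105/1.21 | 0.956 | 93.9% |
| 1.2 | 1.22/1.44 | 0.920 | 92.9% |

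**Unequal arms.** Under 1:1 allocation, k² is replaced by the mean week-12 variance of the two arms. With SD 1.2 in one arm and 1.0 in the other, the mean variance is (1.44+1)/2 = 1.22, v = (1+1.22)/2 = 1.11, and the ratio is sqrt(1.11/1.22) = 0.954. A 2x2 covariance common to both arms already captures this.

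**Simulation.**
- REML random-intercept fits (35 per arm, r = 0.8, 400 trials per scenario, normal-quantile intervals) gave coverage of 95.3% at k = 1, 91.8% at k = 1.2, 97.0% at k = 0.8, and 94.3% with one arm only at 1.2. The Monte Carlo error near 95% is about sqrt(0.95 × 0.05/400) = 1.1 points.
- A second simulation (40 per arm, 1,500 trials per scenario, t intervals on 77 df) gave 92.7% under compound symmetry against 94.5% unstructured at k = 1.2, r = 0.8, and 97.5% under compound symmetry at k = 0.8.

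**Price of the freer model.** With equal variances and r = 0.8, the large-sample SE at 40 per arm is sqrt((2/40) × (1 − 0.64)) = 0.134 baseline SDs under either model. The simulated SEs of the two models were 0.133 and 0.132. When variances differ, the unstructured fit is also slightly more efficient. The true SE under compound symmetry exceeds the unstructured SE by sqrt((1−ρ²)/(1−r²)). At k = 1.2, r = 0.8, ρ = 0.96/1.22 = 0.787 and the factor is sqrt(0.381/0.36) = 1.028.

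**The case against.** The strongest reply is that the article never states the residual covariance. A participant random effect can be combined with visit-specific residual variances, such detail usually sits in an SAP, and an SAP has been posted. This stands. A reader might infer that the plan forces equal variances and that its intervals therefore have the wrong width. The documents do not support that, because the first depends on an unstated residual structure and the second on SDs that nobody has reported.

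The reasons to expect unequal variances are also modest. The entry bounds act directly on BMI and waist, not on fitness, glucose or insulin, which Study Objectives names. On adherence, the Background cites fitness gains of about 4-5%. Taking 5% and an assumed baseline coefficient of variation of 20%, the mean gain is 0.25 SD. If individual gains spread uniformly from zero to 0.5 SD, independent of baseline, the added SD is 0.5/sqrt(12) = 0.14 and the snacks-arm ratio is sqrt(1 + 0.14²) = 1.01. At a coefficient of variation of 10% it is sqrt(1 + 0.29²) = 1.04. Large inflations of the snacks-arm SD, such as 1.5 or 2 times, have no footing in the document.

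A reader might also infer that the SD used to plan the definitive trial will be misstated. No planning SD is given, nothing says it will come from the model's variance components, and group SDs are promised as descriptives for normally distributed outcomes. Sampling error matters too: with 70 participants, the 95% factors for a pooled SD are about 0.86 to 1.20, wider than the 8% shift at k = 1.2.

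What the reply leaves standing is that the participant effect is the only device the article names for the repeated measures, and its ordinary default carries an equal-variance assumption that the trial does not need.

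**Conclusion.** The point holds as a conditional and low-cost improvement. It is not a demonstrated error. If residuals are independent and the week-12 SD differs from baseline, the 12-week CI is miscalibrated: about 8% too narrow at a ratio of 1.2, about 13% too wide at 0.8, and 4-6% off between 0.9 and 1.1. If the SDs are equal, the interval is correct. These sizes rest on assumed SD ratios and on a large-sample calculation with complete data and no site effect, with simulation in reasonable agreement. The primary outcomes are feasibility measures and no stated decision rule uses these intervals, so the consequence is limited to the exploratory efficacy estimates and what is later built on them. If the posted SAP already specifies an unstructured or visit-specific covariance, the modelling part is settled.

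The reporting part stands separately. For outcomes judged non-normal, the article promises median (IQR) only, so no week-12 SD is assured for them, and no within-person correlation is promised for any outcome. Both are useful inputs for sizing the definitive trial.

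**What to change.** 1. Check the posted SAP. If it does not already do so, keep the constrained-baseline means (common baseline mean, separate week-12 means) and replace the participant random intercept with an unstructured 2x2 covariance over the two visits, fitted by REML with small-sample degrees of freedom such as Kenward-Roger. The intercept should be replaced, not added to, because it is not separately identifiable alongside an unstructured 2x2 matrix.
2. For every continuous outcome, including those summarised by median (IQR), report the observed week-12 SD by arm and the baseline-to-week-12 correlation, labelled as planning values for the definitive trial.
3. Letting the week-12 variance differ by arm is optional under 1:1 allocation.

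The cost is a sentence or two of SAP text and one extra covariance parameter. No new data are needed, and precision is essentially unchanged when the variances are equal. The Abstract says analysis starts only after all enrolled participants finish, so the choice can still be fixed or confirmed in advance.

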**Methods:**

A 2-site, parallel arm, RCT will be conducted in Kelowna and Hamilton, Canada. Eighty inactive adults living with obesity will be randomized to an exercise snacks or stretching/mobility exercise comparator group for 12 weeks. The former will complete 4 × 1-minute bouts of vigorous exercise at least 5 days per week, and the latter will perform mobility or stretching exercises using the same schedule. Interventions will be delivered through a customized smartphone mobile app and will be tailored to the participants’ schedules via onboarding counseling sessions, with ongoing telephone check-in call support at weeks 1, 2, 4, and 8. This pilot RCT will focus on feasibility as reflected by rates of recruitment, adherence, and dropout. We will also assess cardiorespiratory fitness, anthropometric markers, and routine blood health markers (eg, glucose, insulin) at baseline and postintervention.

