### Randomization and Blinding

The randomization of participants will occur during the second baseline testing visit after the collection of baseline measures. Participants will be randomized using a 1:1 allocation ratio with variable permuted block sizes (stratified by sex and site) through the web-based platform REDCap (Research Electronic Data Capture) tools hosted at the UBC (Research Electronic Data Capture, Nashville, USA) [29,30]. A researcher not involved in the project created the randomization sequence. When a new participant completes baseline testing and is ready for randomization, the participant’s sex and site will be entered by the researcher into REDCap, which will display the randomization (exercise snacks, stretching exercise comparator) for that participant. Due to the nature of the intervention, blinding of the participants or the researchers delivering the intervention is not possible.

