## Results

This study is funded through the Heart & Stroke Foundation of Canada Grants-in-Aid program (2024/2025). Recruitment began on July 18, 2025 (following trial registration), at UBC Okanagan and in November 2025 at McMaster University. As of March 31, 2026, we have enrolled 65 participants (UBC, n=51; McMaster University, n=14).

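### With two sites, site belongs in the mixed model as a fixed effect, and sex, the other stratification factor, should join it; a near-free improvement with low stakes

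*Protocol article*

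**What the plan says.** Statistical Analysis in the protocol article names the model for continuous outcomes: a constrained baseline longitudinal analysis by "linear mixed models with group and time as fixed effects and participant and study site as random effects". The target is the between-group difference at 12 weeks, reported with a 95% CI and a preliminary effect size. The analyses are labelled exploratory.

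The design uses two stratification factors. Trial Design gives "1:1 allocation ratio stratified by sex and site", and Randomization and Blinding repeats it with "variable permuted block sizes (stratified by sex and site". The Abstract fixes the number of sites: "A 2-site, parallel arm, RCT will be conducted in Kelowna and Hamilton, Canada". Results reports uneven accrual to March 31, 2026: "we have enrolled 65 participants (UBC, n=51; McMaster University, n=14". The target is 40 per group, 80 in total (Participants and Eligibility Criteria).

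Sex is not in the stated model, and the article describes no other adjustment for it. The article says that an SAP was posted on April 30, 2026; it was not available for this review.

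**The concern.** A random site effect asks the data for a variance across sites. Two sites supply one difference, so one degree of freedom. The estimate will often fall on the boundary at zero, where site has no effect on the fit, and software may report a singular fit. Textbox 2 lists 11 secondary outcomes. Under this model site would be adjusted for in some of them and effectively not in others, according to a boundary estimate and not the plan.

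Factors used to restrict randomisation are normally carried into the analysis. If a prognostic stratifier is left out, the model-based standard error ignores the balance that stratification created and tends to be too large. Several outcomes plausibly differ by sex, such as grip strength, weight and waist; the waist thresholds for entry are themselves sex-specific.

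At stake are the stability and uniformity of the models and a little precision in the effect estimates meant to inform a definitive trial.

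**Working it through.** The article gives no power, SD or effect-size figure that depends on this model, so there is no planned figure to reproduce. The checks below size the consequence.

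**1. Precision of a site SD on 1 df.** The 95% limits, as multiples of the estimate, are √(1/χ²) at the 97.5% and 2.5% points on 1 df:
- lower: √(1/5.024) = 0.446
- upper: √(1/0.000982) = 31.9

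So the interval runs from about 0.45 to 32 times the estimate.

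**2. How often the site variance is estimated as zero.** Scaling 51:14 to 80 gives 80 × 51/65 = 62.8 and 80 × 14/65 = 17.2. The calculation uses 62:18 as an assumption. In units of the residual variance:
- sampling variance of the site difference: 1/62 + 1/18 = 80/(62 × 18) = 0.0717
- a true site SD of τ residual SDs adds 2τ²
- the estimate is zero when the squared observed difference is below 0.0717, so the probability is P(χ² on 1 df < 0.0717/(0.0717 + 2τ²))

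| True site SD (residual SDs) | 2τ² | Ratio | P(estimate is zero) |
|---|---|---|---|
| 0 | 0 | 1 | 0.68 |
| 0.2 | 0.08 | 0.473 | 0.51 |
| 0.4 | 0.32 | 0.183 | 0.33 |

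A 63:17 split gives 0.68, 0.51 and 0.34.

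A REML simulation of the stated model agrees in direction. It assumed N = 80 split 62:18, 12.5% loss, correlation 0.5 or 0.8, and 100 runs per setting. The site variance was effectively zero in 71 to 75% of runs with no site difference, and in 15 to 29% with a site difference of 0.5 SD.

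**3. Effect of random versus fixed site on the treatment estimate.** A second simulation used the same N, split, loss and correlations, arms balanced within site, a constant site shift of 0, 0.5 or 1 SD, and 40 runs per setting. The two estimates differed by 0.0003 to 0.0024 SD on average (95th percentile at most 0.005 SD), against standard errors of about 0.14 to 0.20. The ratio of standard errors lay between 0.997 and 1.0004. With a single optimiser start some fits were poor (ratio up to 1.37); several starts removed these. A site difference that changes over time was not tested.

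**4. Cost of omitting sex.** Assume equal numbers of each sex, a constant sex effect of s SDs, within-sex variance 1 and within-person correlation ρ. With sex in the model, the residual variance at 12 weeks given baseline is 1 − ρ². Without it, the variance is 1 + s²/4 and the covariance ρ + s²/4. The residual variance becomes (1 + s²/4) − (ρ + s²/4)²/(1 + s²/4), and the SE ratio is the square root of the quotient.

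| s | ρ | Without sex | With sex | SE ratio | Simulated SEs (ratio) |
|---|---|---|---|---|---|
| 1 | 0.5 | 0.800 | 0.750 | 1.03 | 0.211 / 0.204 (1.03) |
| 2 | 0.5 | 0.875 | 0.750 | 1.08 | 0.221 / 0.204 (1.08) |
| 1 | 0.8 | 0.368 | 0.360 | 1.01 | 0.143 / 0.142 (1.01) |
| 2 | 0.8 | 0.380 | 0.360 | 1.03 | 0.145 / 0.142 (1.02) |

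The simulated column comes from the simulation in step 2 and compares the stated model with one holding both site and sex as fixed effects. Type I error was 0.04 to 0.06 under both models; with 100 runs that is imprecise.

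**The case against.** The strongest reply is that steps 1 and 2 describe a nuisance parameter that the trial never proposes to report. Allocation is 1:1 within site, so group is nearly orthogonal to site. The variance goes to zero when the observed site difference is small, which is when adjustment matters least. This stands: for a constant site shift, step 3 shows almost no movement in the estimate or its standard error. What remains is numerical instability and adjustment that varies by outcome.

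The second reply is that the repeated baseline already absorbs most of any constant sex difference. This also stands. The 8% needs a 2 SD sex effect with a correlation of only 0.5; at 0.8 the loss is about 1 to 3%.

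The third is that a covariate list is commonly left to the SAP, which may include sex. This stands in part. The article does not leave the model open: it names the fixed and random effects. Random site is a stated choice, and sex is missing from a stated list that sits beside a design stratified on it. If the SAP already includes sex, the two documents differ and need reconciling.

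A reader might infer that the treatment effect will be biased, that its intervals will be too narrow, or that the strata are ignored altogether. The documents support none of these. Site is in the model, allocation is balanced within strata, and the error from omitting sex is in the conservative direction.

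**Conclusion.** The point holds as a specification weakness with small consequences. A two-level random site effect gives a very imprecise variance that is often zero: about 68% of the time with no true site difference, and 51% or 33% if the true site SD is 0.2 or 0.4 residual SDs, assuming a 62:18 split. Omitting sex widens the intervals by about 1 to 8% for sex effects of 1 to 2 SD and correlations of 0.5 to 0.8. The split extrapolates current enrolment; the sex effects, correlations and loss are assumptions, because the article gives no such figures.

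It would go too far to say that the site variance cannot be estimated at all or that the 12-week comparison is invalid. The primary outcomes are feasibility counts and percentages, which this model does not touch, and the sample size does not rest on it. This is a free improvement with low stakes.

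**What to change.** Specify, in the article's Statistical Analysis and in the SAP: fixed effects for time, group at 12 weeks (common baseline mean retained), site and sex, with participant as the only random effect; or an unstructured 2 × 2 within-participant covariance in place of the random effect. Use the same model for every continuous outcome. If the posted SAP already differs from the article, say which governs and align the two.

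The cost is one line of text and two fixed-effect degrees of freedom out of about 80 participants. Site and sex are already recorded at randomisation, so no data collection changes. By the Abstract, analysis starts only after all enrolled participants have finished, so the change can still be made as a dated amendment before then.
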